### Randomisation and blinding

The statisticians of Kyung Hee University Centre for Clinical Research and Drug Development (KCRD), the Contract Research Organisation (CRO), will generate random sequences using the SAS program. KCRD will send the random number cards to each institution. Randomisation procedures will be performed at visit 2, using a random number card in a black envelope. The subjects in this trial will be assigned to one of two groups with an allocation ratio of 1:1. All participants, investigators, and monitors will be blinded. No one, with the exception of the statisticians at KCRD, will be aware of which random number refers to either the treatment group or the placebo group. The randomisation table kept in the opaque sealed envelope by the CRO should be opened according to Standard Operating Procedures (SOPs).

### Treatment protocol

The participants will receive either Euiiyin-tang or a placebo drug for 12 weeks. They will be orally administered 3 g of treatment granules with water three times a day after meals for 12 weeks. The daily dosage adheres to guidelines established by the Ministry of Food and Drug Safety (MFDS) regarding dosage and administration of Euiiyin-tang. The participants will be required to return any drug remains in order to calculate compliance. During the trial, the participants will be prohibited from receiving other weight loss treatment.

### Interventions

Euiiyin-tang is a traditional preparation in Korean medicine. It has been approved as a Korean herbal medicine by the Korean MFDS. The intervention consists of 1.7 g Euiiyin-tang soft extract (including 1.33 g *Ephedra sinica stapf*, 1.33 g *Angelica gigantis radix*, 1.33 g *Atractylodis rhizoma alba*, 3.33 g *Coicis Semen*, 1.00 g *Cinnamomi cortex*, 1.00 g *Paeoniae radix alba*, and 0.67 g *Glycyrrhiza uralensis*), 1.15 g lactose hydrates, and 0.83 g corn starch. Euiiyin-tang is categorised as ‘Other analgesics and antipyretics’ by Anatomical Therapeutic Chemical (ATC) code N02BG. The placebo medicine consists of lactose, corn starch, and food colourings, and possesses an appearance, shape, weight, taste, and colour similar to Euiiyin-tang. The treatment drug and placebo will be supplied by Hanpoong Pharm & Foods Co., Ltd.

### Primary outcome measurement

The primary outcome in the present study is the change in weight of participants between baseline (visit 2) and post-treatment (visit 5).

### Secondary outcome measurements

The secondary outcomes include the average weight reduction during the visits and among the groups, and changes in body fat, waist and hip circumferences, and waist-to-hip ratio (WHR). In addition, the secondary endpoints include changes in BMI, lipid profile, C-reactive protein (CRP), visceral fat, and glucose, and questionnaire responses to the Korean version of Obesity-related Quality of Life (KOQOL) [25], the Korean version of Eating Attitudes Test KEAT-26 [26], the Social Readjustment Rating Scale (SRRS) [27], and the Stress Reaction Inventory (SRI) [28]. The QSCCII responses will also be assessed. The Standard Protocol Items: Recommendations for Interventional Trials (SPIRIT) study schedule is detailed in Fig. 2.

**Fig. 2 Fig2:**
[figure not shown]
SPIRIT schedule for the trial

### Safety outcomes

All variables related to the safety assessment of the study such as vital signs, physical examination, and various laboratory test results, including haematologic test, biochemical test, and urine test, as well as adverse events will be documented on the case report form (CRF) at every visit.

### Statistical analysis

#### Efficacy assessment

The demographic data at the baseline will be analysed using a *t* test for continuous data and a chi-square test for categorical data. Analysis of the primary endpoint will be performed using intention-to-treat (ITT) datasets. Per-protocol (PP) datasets will also be analysed as a reference. The term ITT dataset refers to a set of data regarding all randomly assigned participants. Missing data will be assigned using the last-observation-carried-forward (LOCF) analysis method. PP datasets include data on only the participants who completed the trial with no protocol violations or deviations.

The secondary endpoint data will be analysed using both ITT and PP datasets. The average weight change before and after treatment will be analysed using a paired *t* test for intragroup data and a Student’s *t* test for intergroup data. The average weight during the treatment phase will be analysed using repeated measures analysis of variance (ANOVA) tests. Other secondary data will be analysed identically to the average weight change, with the exception of glucose measurements and questionnaire results, which will be compared only before and after treatment between the groups. The present study has no plan for an interim analysis.

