### Subject withdrawal criteria

The subject withdrawal criteria are as follows: detection of eligibility violations; occurrence of a serious adverse event; subject has an acute reaction (such as allergy or shock) due to administration of the investigational product; detection of a systemic disease that was not discovered at the screening stage; less than 70% compliance; subject’s withdrawal of consent; use of any forbidden medication or treatment during the trial that could affect the study result; uncooperative subject; occurrence of other significant protocol violations; subject who cannot follow up; subject unable to progress because of worsening of pre-existing disease; investigator’s decision to terminate the process for the sake of the subject’s health. The participants who are withdrawn after randomisation will be followed up to examine outcomes.

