### Sample size

The sample size calculation is based on weight change between baseline (visit 2) and after treatment (visit 5). The hypothesis is as follows:$$ {\mathrm{H}}_0:\updelta =\Delta 1\hbox{-} \Delta 2=0 $$
$$ {\mathrm{H}}_1:\updelta =\Delta 1\hbox{-} \Delta 2\ne 0 $$where Δ1 = Weight change between visit 5 and baseline in Euiiyin-tang group

Δ2 = Weight change between visit 5 and baseline in placebo control group.

In a study by Heymsfield et al. [23], the standard deviation (SD) in weight reduction of the groups is 3.9. We assume that both groups will have an equivalent SD. The effect size of this study is hypothesised to be 0.5 as the moderate effect. Consequently, the difference in weight change between groups is assumed to be 1.95. The allocation ratio is 1:1. The following formula is used to estimate the sample size [24]:$$ \mathrm{m}=\left(\frac{1+\psi}{\psi}\right)\kern0.24em \frac{{\left({\mathrm{z}}_{1\hbox{-} \frac{\upalpha}{2}}+{\mathrm{z}}_{1\hbox{-} \beta}\right)}^2}{\varDelta^2}+\frac{{{\mathrm{z}}^2}_{1\hbox{-} \frac{\upalpha}{2}}}{2\left(1+\psi \right)} $$where *m* = the sample size of one group$$ \uppsi =\mathrm{the}\;\mathrm{allocation}\;\mathrm{ratio} $$
$$ \upalpha =0.05,\upbeta =0.8 $$

After taking into account the dropout rate of approximately 20%, the sample size for each group is 80 participants, to allow the test to remain within 5% of the two-sided significance level and possess 80% statistical power. Therefore, the total sample size of this trial is 160.

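### LOCF as the primary missing-data method can create or shrink a weight difference if weight falls over the 12 weeks, and the plan does not tie it to the post-withdrawal weights it intends to collect

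*Protocol article*

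**What the plan says.** All references are to the protocol article. Under Primary outcome measurement, the endpoint is weight change from visit 2 to visit 5, after 12 weeks of treatment. Under Efficacy assessment:

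- "Analysis of the primary endpoint will be performed using intention-to-treat (ITT) datasets", and this set is defined as everyone randomised.
- For gaps in the data, the rule is: "Missing data will be assigned using the last-observation-carried-forward (LOCF) analysis method".
- The only other stated analysis of the primary endpoint is per-protocol, for reference: "PP datasets include data on only the participants who completed the trial with no protocol violations or deviations".
- Among the secondary analyses: "The average weight during the treatment phase will be analysed using repeated measures analysis of variance (ANOVA) tests".

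Three other places bear on the point. Sample size allows for roughly 20% dropout and does not split it by arm. Table 1 requires agreement to a low-calorie diet. Subject withdrawal criteria lists serious adverse events, acute reactions to the product and compliance under 70% among the reasons for withdrawal, and then adds: "The participants who are withdrawn after randomisation will be followed up to examine outcomes".

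**The concern.** LOCF enters a participant's last recorded weight as the visit-5 weight. That is accurate only if weight would not have moved afterwards. In a weight-loss trial with a diet in both arms, continuing loss is the more natural expectation, so each carried-forward value probably understates 12-week loss. At 20% dropout that could affect about 32 of 160 participants (0.20 × 160).

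The understatement need not be equal in the two arms, because several withdrawal reasons may act differently on active and placebo. If more placebo participants leave, LOCF can produce a benefit where there is none. If more active participants leave, it can hide a real one. The direction is unknown in advance, so LOCF cannot be defended as conservative. The per-protocol analysis drops non-completers and so does not test the LOCF assumption. Nor does the analysis section say that weights obtained after withdrawal take precedence over carried-forward ones.

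**Working it through.** **Plan's own figure.** With allocation ratio 1 and effect size 0.5, the Sample size formula gives 2(1.960 + 0.842)²/0.25 + 1.960²/4 = 62.79 + 0.96 = 63.75, rounded up to 64. Then 64/0.80 = 80 per group. The stated 160 is reproduced.

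**Inputs from the article.** 80 per arm; SD 3.9; difference δ = 1.95; two-sided α = 0.05; about 20% dropout overall.

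**Assumptions (not in the article).** Units are kg. Loss is linear to week 12, P = 3 kg on placebo and P + δ on active. Visits are evenly spaced. Dropouts leave after visit 2, 3 or 4 with equal probability, so they carry forward 0, 1/3 or 2/3 of their 12-week loss (mean f = 1/3). Had they stayed under observation, they would have continued on their arm's slope.

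**Formula.** With dropout d_T (active) and d_C (placebo), the expected LOCF difference is

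(P + δ)[1 − d_T(1 − f)] − P[1 − d_C(1 − f)].

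**No drug effect (δ = 0).** This reduces to P(1 − f)(d_C − d_T) = 2(d_C − d_T). Rejection rates come from simulating 20,000 trials with a two-sample t test.

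| Active/placebo dropout | False benefit | Type I error |
|---|---|---|
| 20%/20% | 0 kg | about 5% |
| 15%/25% | 0.2 kg | about 6% |
| 10%/30% | 0.4 kg | 10–11% |

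Reversing a split reverses the sign. For the 10%/30% split, P = 2 to 4 kg gives 0.27 to 0.53 kg and type I error of 7.5% to 15%.

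**True effect 1.95 kg.**

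| Active/placebo dropout | LOCF difference | Power |
|---|---|---|
| 20%/20% | 4.95 × 0.867 − 3 × 0.867 = 1.69 kg | about 80% |
| 25%/15% | 4.95 × 0.833 − 3 × 0.900 = 1.43 kg | about 66% |
| 30%/10% | 4.95 × 0.800 − 3 × 0.933 = 1.16 kg | about 48% |
| 15%/25% | 4.95 × 0.900 − 3 × 0.833 = 1.96 kg | about 91% |
| 10%/30% | 4.95 × 0.933 − 3 × 0.800 = 2.22 kg | about 96% |

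With true week-12 weights for all 80 per arm, the estimate is 1.95 kg and power is 88%.

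**If dropouts instead return to baseline weight.** The actual week-12 difference over all randomised is (P + δ)(1 − d_T) − P(1 − d_C). At 20%/20% it is 4.95 × 0.80 − 3 × 0.80 = 1.56 kg; LOCF gives about 1.69 and a likelihood-based repeated-measures model about 1.95. At 25%/15% it is 4.95 × 0.75 − 3 × 0.85 = 1.16 kg, against about 1.4 for LOCF and 1.92 for the model.

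**The case against.** **The size is assumption-driven.** This stands. The article gives no weight trajectory and no dropout by arm, and the visit schedule figure is not shown. Nothing points to a threefold difference in dropout. At 17.5%/22.5% with no effect, the false benefit is only about 0.1 kg and type I error 5–5.5%. At equal 20% dropout, power under LOCF is still close to the planned 80%.

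**Unequal dropout always biases the result.** A reader might infer this, but it does not hold. With a true effect, 15%/25% returns 1.96 kg because two errors cancel, while equal dropout shrinks the estimate. Only with no true effect does unequal dropout by itself produce a false difference, and then only if weight is falling.

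**The LOCF standard error is wrong.** This is also tempting and is not shown. Each participant contributes one value, and type I error is about 5% at equal dropout. The inflation elsewhere comes from a shift in the mean.

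**A repeated-measures model is not automatically better.** This stands. Its advantage in the main scenarios follows from letting dropouts stay on their arm's slope. If they return to baseline, LOCF is the closer of the two to the all-randomised difference.

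**Follow-up after withdrawal may solve much of this.** It may: a visit-5 weight that is obtained is not missing. The full protocol or SAP may make the link, so the lack of that detail in an article is not itself the fault. The fault is that the article fixes LOCF as the method for whatever remains missing.

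**Conclusion.** The point holds in a limited form. LOCF is the stated method for the primary comparison and fits the endpoint badly if weight falls over the 12 weeks. With no drug effect, unequal dropout then produces a false difference: small at moderate imbalance, and enough to double the type I error at 10%/30%. With a real effect LOCF usually distorts the estimate, cutting it by about 13% at equal 20% dropout (1.69/1.95 = 0.87) and by more when dropout is higher on active.

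These sizes rest on the assumed linear loss, the 3 kg placebo loss, the dropout timing and the splits by arm. They show what the rule can do, not what will happen in this trial. Whether LOCF also feeds the repeated-measures ANOVA is a reading of one general missing-data sentence; if it does, that analysis has the same weakness.

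**What to change.** In Efficacy assessment:

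1. State that every observed visit-5 weight, including those collected after withdrawal, enters the primary analysis and is never replaced by a carried-forward value.
2. Replace LOCF as the primary method with a likelihood-based repeated-measures model of weight change at the post-baseline visits in all randomised participants. Include treatment, visit, treatment-by-visit, baseline weight and centre, and take the visit-5 treatment contrast as the primary effect. The same model can serve in place of the repeated-measures ANOVA.
3. Add a reference-based (placebo-based) imputation as a sensitivity analysis. The model assumes missing at random and would overstate the effect if dropouts regain weight.
4. Keep LOCF at most as a further sensitivity analysis.

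Make and date the change before unblinding; Trial status reports 149 recruited and no interim analysis is planned. The cost is analysis wording only: no extra participants, and no measurements beyond the follow-up already planned. The downside is a somewhat larger standard error and reliance on missing at random for weights never obtained.

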## Methods/design

### Study design

The present study is a randomised, double-blinded, parallel-group, placebo-controlled multi-centre trial taking place at the following three hospitals: Gachon University Gil Medical Center in Incheon, Seoul St. Mary’s Hospital, and Sangji University Korean Medicine Hospital in Wonju. Participants will be outpatients of these institutions. Any participant fulfilling the eligibility criteria will be included in the study. This study will have two arms: the Euiiyin-tang treatment group and the placebo treatment group. Figure 1 presents an overview of the trial. Protocol amendments are not expected. However, if necessary, any modification to the protocol will be reported to the entire investigational team through a conference. All changes will be included in the final manuscript prior to journal submission.

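### Between-group comparisons of change use an unadjusted Student's t test; adding the baseline value and centre as covariates would gain some precision at almost no cost

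*Protocol article*

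**What the plan says.** The Efficacy assessment section of the protocol article states that weight change before and after treatment is compared within groups by a paired t test and between groups by "a Student’s *t* test for intergroup data". It continues: "Other secondary data will be analysed identically to the average weight change". Glucose and the questionnaire results are excepted; they are compared before and after treatment between the groups, and no test or adjustment is named. Weight over the treatment phase is analysed by repeated measures ANOVA, with no covariates named.

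The t test sentence stands in the paragraph on secondary endpoints. The paragraph on the primary endpoint gives only the datasets and the handling of missing data. The primary outcome is the same quantity, weight change from visit 2 to visit 5, so this is the only between-group test that the article gives for it.

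The Study design section describes a "placebo-controlled multi-centre trial taking place at the following three hospitals". Under Randomisation and blinding, random number cards go to each institution; stratification by centre is not stated. Centre appears in no efficacy analysis.

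The Sample size section rests on the same unadjusted contrast of change: "the standard deviation (SD) in weight reduction of the groups is 3.9", "The effect size of this study is hypothesised to be 0.5 as the moderate effect", and so "the difference in weight change between groups is assumed to be 1.95".

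**The concern.** A change score subtracts the baseline value with a fixed slope of 1. The true slope of the visit-5 value on baseline is usually below 1, so change remains correlated with baseline. Two things follow. Variance that baseline could explain stays in the error term, and part of any chance difference in baseline between the groups carries over into the estimated effect.

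Baseline weight will vary, because entry combines BMI of 30 or more with BMI 27 to 29.9 plus a risk factor. The article plans tests of baseline demographic data between the groups but names no adjustment that would deal with an imbalance. A covariate fixed in advance would do so and would leave no room for choosing covariates after the data are seen. The design targets 80% power with no margin beyond the dropout allowance, so precision available from data already collected is worth having.

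**Working it through.** **1. Inputs from the Sample size section.** Two-sided alpha 0.05, power 80%, SD of change 3.9, effect size d = 0.5, difference 0.5 × 3.9 = 1.95, allocation 1:1 (ψ = 1), dropout 20%. The line under the formula prints β = 0.8; I read this as the power, as the text states 80%. No unit is printed for 3.9 and 1.95; I take them as kg.

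**2. The plan's own figure.**

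m = [(1+ψ)/ψ] × (z₀.₉₇₅ + z₀.₈₀)² / d² + z₀.₉₇₅² / [2(1+ψ)]

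= 2 × (1.960 + 0.842)² / 0.25 + 1.960² / 4 = 63.75, so 64 per group.

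64 / (1 − 0.20) = 80 per group, 160 in total. This matches the article. Noncentral-t power of the unadjusted test at 64 per group is 80.1%.

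**3. Variance with and without baseline adjustment.** With the same SD σ at both visits and pre-post correlation ρ:

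- variance of change = 2σ²(1 − ρ)
- residual variance after regression on baseline = σ²(1 − ρ²)
- ratio = (1 + ρ)/2, so the share of the variance in change that baseline explains is R² = (1 − ρ)/2.

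**4. Weight.** The article gives neither σ nor ρ. I assume σ of 8 to 15 kg, equal at both visits. Then ρ = 1 − 3.9²/(2σ²), the residual SD is 3.9 × √(1 − R²), and power is computed at 64 per group for a difference of 1.95, with 3 degrees of freedom spent (one for baseline, two for three centres).

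| σ (kg, assumed) | ρ | R² from baseline | Power |
|---|---|---|---|
| 8 | 0.881 | 5.9% | 82.5% |
| 10 | 0.924 | 3.8% | 81.6% |
| 12 | 0.947 | 2.6% | 81.2% |
| 15 | 0.966 | 1.7% | 80.8% |

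If the covariates explain nothing, power goes from 80.15% to 80.13%. If baseline and centre together explained 10%, it would be 84.1%; nothing in the article supports a particular value.

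**5. Carry-over of a baseline imbalance.** With σ = 10 kg and 80 per group, one standard error of the baseline difference is 10 × √(2/80) = 1.58 kg. If baseline and change correlate at 0.1 to 0.3 in magnitude (assumption), the slope of change on baseline is 0.039 to 0.117 (0.1 × 3.9/10 to 0.3 × 3.9/10). The shift is 1.58 × 0.039 = 0.06 kg to 1.58 × 0.117 = 0.18 kg, or 3 to 9% of 1.95.

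**6. Less stable outcomes.** For assumed ρ of 0.5, 0.6 and 0.7, (1 + ρ)/2 = 0.75, 0.80 and 0.85: a variance reduction of 25%, 20% and 15%.

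**7. Centre.** The article gives no between-centre variance, so the gain from centre cannot be computed.

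**The case against.** The strongest reply is that nothing here is wrong. Under 1:1 randomisation a t test on change is unbiased and keeps its error rate, and it is the test that the sample size assumes. That stands, and the point is confined to precision.

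Four stronger readings are tempting and fail:

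- *Baseline is ignored, so an imbalance passes straight into the effect.* The outcome is change from visit 2, so baseline is already subtracted. Only the slope of change on baseline carries an imbalance through, about 4 to 12% of it under the correlations assumed above.
- *Every continuous secondary endpoint is compared by this t test.* Glucose and the questionnaires are expressly excepted, and weight over the treatment phase has repeated measures ANOVA.
- *Centre must be in the model because randomisation was stratified by it.* Sending cards to each institution does not establish stratification. The case for centre is only possible precision in a three-hospital trial.
- *The trial is underpowered without adjustment.* The stated size reproduces. The main analysis set is all randomised participants with last observation carried forward, nominally 80 per group. If the assumed difference and SD held there, unadjusted power would be 88.2% and the gain smaller still (89.3% at σ = 10 kg).

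It can also be said that applying the t test to the primary endpoint is an inference in a condensed article. That is fair, but the quantity is the same and no other between-group test of it is given.

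**Conclusion.** The point holds as a free improvement, not as an error. The article fixes an unadjusted test of change for weight and most secondary outcomes, where adjusting for baseline would be at least as precise apart from a negligible loss of degrees of freedom. For the primary endpoint the expected gain is small, about 1 to 2.5 power points. This rests on equal weight SDs of 8 to 15 kg at both visits, which the article does not give, together with its stated SD of change. The gain is larger for outcomes that track less closely over 12 weeks: 15 to 25% of the variance at assumed correlations of 0.7 to 0.5. The direction is secure; the size depends on those assumptions. The validity of the planned test and the stated sample size are not in question.

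**What to change.** Before unblinding, replace the between-group Student's t test with a linear model of the visit-5 value (or of change) on treatment and the baseline value of the same variable, with centre as a further covariate. Use it for the primary endpoint and the continuous secondary endpoints, and state it explicitly in the primary-endpoint paragraph. Report the adjusted difference with its 95% CI.

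The cost is a change of wording and 3 degrees of freedom (126 to 123 at 64 per group). Baseline weight and hospital are already recorded, and the sample size need not change.

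### The repeated-measures ANOVA on weight, filled in by LOCF, is a weak test of a secondary outcome that the article defines as weight reduction

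*Protocol article*

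**What the plan says.** Under Secondary outcome measurements, the Protocol article lists "the average weight reduction during the visits and among the groups". Under Efficacy assessment, it assigns the method: "The average weight during the treatment phase will be analysed using repeated measures analysis of variance (ANOVA) tests". The same section gives the rule for incomplete data: "Missing data will be assigned using the last-observation-carried-forward (LOCF) analysis method".

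Weight change from before to after treatment has its own tests; it is "analysed using a paired *t* test for intragroup data and a Student’s *t* test for intergroup data". The primary outcome and the sample size both rest on the change from visit 2 to visit 5.

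The ANOVA sentence does not say which term (group, visit or group-by-visit) is the treatment test, whether visit 2 counts as one of the repeated measures, or whether a sphericity correction is applied. Under Subject withdrawal criteria, the article says that participants withdrawn after randomisation are still followed for outcomes.

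**The concern.** The method and the outcome scale are stated, so this is more than a detail left for later. Three features of that choice are weak.

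- **Scale.** On weight itself, a comparison of group averages is made against stable differences in body size between women. The entry criteria set a lower BMI limit and no upper one, so those differences are likely to be large relative to a difference of 1.95.
- **Visits.** The wording points to the treatment phase, which can be read as visits 3 to 5. A group-by-visit test on those visits asks only whether the groups are still diverging, not whether they differ.
- **Missing data.** A classical repeated-measures ANOVA needs a complete series for each person. LOCF supplies it by treating carried-forward weights as measurements, although later weights may have been collected.

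This is the planned analysis of weight over the visits. A real effect could go undetected in it, and the result could then sit awkwardly beside the visit-5 comparison.

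**Working it through.** **Inputs from the article (Sample size).** The article states that "the standard deviation (SD) in weight reduction of the groups is 3.9" (no unit given; kg assumed). The difference is 1.95, the effect size 0.5, allocation 1:1, two-sided 5%, power 80%, dropout about 20%, 80 per group.

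**Assumptions, not in the article.** Between-person weight SD 6 to 15 kg; visits 2 to 5 equally spaced; effect building linearly (0, 0.65, 1.30, 1.95) unless stated; within-person residual SD 0.5 kg unless stated; covariance between visits as named below.

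**Step 1: the plan's own figure.** m = 2(1.960 + 0.842)²/0.5² + 1.960²/4 = 63.75, so 64; 64/0.80 = 80 per group. This reproduces. A t test on change has 80% power at 64 per group and 88% at 80.

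**Step 2: group main effect on weight.** The average difference is 3.90/4 = 0.975 over visits 2 to 5, and 3.90/3 = 1.30 over visits 3 to 5. Power is from the noncentral t with 158 df and noncentrality (d/s)√(n/2), where s is the SD of a person's average weight. Example: weight SD 10 kg, visits 3 to 5, s = 10.33, so 1.30/10.33 × √40 = 0.80 and power is 12%.

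| Weight SD (kg) | Visits 2–5 | Visits 3–5 |
|---|---|---|
| 6 | 16% | 24% |
| 8 | 12% | 16% |
| 10 | 9% | 12% |
| 12 | 8% | 10% |
| 15 | 7% | 8% |

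If 6 kg is taken as the SD of the visit 3–5 average itself, the last column rises to 28%. The range is therefore about 7 to 28%.

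**Step 3: average change from baseline (visits 3–5 minus visit 2).** The SD is 2.62 under random slopes and 2.82 under a random walk. Noncentrality is 1.30/2.62 × √40 = 3.14 and 1.30/2.82 × √40 = 2.91, giving 88% and 83% power at 80 per group. Compound symmetry is an unfavourable limit: it needs a residual variance of 3.9²/2 = 7.605, so the variance of average change is 7.605 × 4/3 = 10.14, the SD 3.18, the noncentrality 2.58 and power about 73%.

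**Step 4: type I error of an uncorrected group-by-visit test.** At the lowest possible epsilon, 1/(k−1), the ceiling is P(F(1,158) > 2.62) = 10.7% with four visits and P(F(1,158) > 3.02) = 8.4% with three. Simulation (80 per group, 10,000 runs per scenario) gave:

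| Covariance | Visits 2–5 | Same, 20% LOCF | Visits 3–5 |
|---|---|---|---|
| Compound symmetry | 4.9% | 5.0% | 5.0% |
| Random walk | 7.0% | 6.9% | 5.7% |
| Mixed | 7.9% | 8.3% | 6.2% |
| Almost pure random slopes | 9.9% | 10.6% | 8.1% |

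With the Greenhouse-Geisser correction, the visit 2–5 test stayed at 4.7 to 5.2% throughout, with power of 80 to 88% at 80 per group.

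**Step 5: power if only visits 3 to 5 enter.** Simulation with 80 per group, random slopes, weight SD 10 kg, residual SD 0.5 to 1.0 kg, 2,000 runs per scenario:

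| Effect at visits 3, 4, 5 | Group-by-visit (corrected) | Group main effect | Average change from baseline |
|---|---|---|---|
| 0.65, 1.30, 1.95 | 82–88% | about 13% | 86–88% |
| 1.3, 1.7, 1.95 | 28–35% | 16–17% | 97–99% |
| 1.95, 1.95, 1.95 | about 5% | 20–23% | over 99% |

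With baseline as a repeated measure the interaction test does not share this weakness, because the early change is then part of the interaction.

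**Step 6: reach of LOCF.** 0.20 × 160 = 32, so up to about 32 series could contain carried-forward values.

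**The case against.** The strongest reply is that the article leaves open most of what would do harm. A reader might infer that the plan inflates the group-by-visit error rate to about 10% and makes a nearly powerless group main effect the treatment test. The article supports neither inference.

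- About 10% requires no sphericity correction, visit 2 counted as a repeated measure, and almost pure random slopes, all together. Other structures give 5 to 8%. The article does not exclude a correction, and that detail commonly belongs in a statistical analysis plan.
- The group main effect is nowhere named as the treatment test. With baseline included, the usual test is group-by-visit, which keeps roughly the design power.
- The 10% figure needs visits 2 to 5, while the most natural reading of the treatment phase is visits 3 to 5, where the ceiling is 8.4%.
- The ANOVA sentence may be condensed wording for weight reduction over the visits, as the outcome definition says.
- LOCF changes the simulated error rate by less than one percentage point.

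All of this limits the size of the point. What remains is that the analysis text names weight while the outcome is a reduction, and that on weight at visits 3 to 5 neither ANOVA test can be relied on if the effect comes early. The small effect of LOCF on the error rate does not make carried-forward values measurements, and the article plans follow-up that could supply real ones.

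**Conclusion.** The point holds as a weakness in how a secondary analysis is specified. On weight, a group main effect has about 7 to 28% power for the planned effect. Average change from baseline has 83 to 88% under random-slope or random-walk covariance, and about 73% in the compound-symmetry limit. Restricted to visits 3 to 5, the group-by-visit test falls from over 80% power to about 5% as the effect moves from linear build-up to complete by visit 3. With baseline included it keeps roughly the design power. Error-rate inflation is conditional: from 5% up to a ceiling of 10.7% (8.4% with three visits), and only if no correction is used.

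These sizes rest on assumed weight SDs, visit spacing, effect shapes and covariance structures; only the SD of change, the difference, the dropout rate and the sample size come from the article. The visit-5 t test and the sample size do not depend on this analysis.

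**What to change.** Replace the ANOVA sentence with a mixed model for repeated measures on change in weight at visits 3, 4 and 5. Include treatment, visit, treatment-by-visit, baseline weight and baseline-by-visit, with unstructured covariance. Fit it to all observed weights, including those collected after withdrawal, without LOCF. Report two treatment contrasts: at visit 5, and averaged over visits 3 to 5.

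If ANOVA is kept, analyse change from baseline, apply the Greenhouse-Geisser correction, and report the group contrast on average change. That contrast must be named: subtracting baseline leaves the group-by-visit test on visits 3 to 5 exactly as it was, so moving to change helps only through the group comparison.

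The cost is revised wording and a few lines of code, with no new data. The downside is a few more covariance parameters and a missing-at-random assumption for weights that are never observed.
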